## Discussion

This is the first study to explore the potential use of a MMIEAD for kidney cachexia; therefore, a feasibility study is appropriate to test (and potentially refine) the intervention components and their efficacy, while addressing the relevant questions surrounding feasibility [42]. Sample size for quantitative and qualitative analyses is often contended in feasibility studies as are the parameters around progression to a definitive RCT. Adherence to Pearson and colleagues [69], guidance regarding aims, methods, design, measures appropriate for those undertaking formative feasibility, or pilot studies in the field of implementation science has been previously described in the “Methods/design” section of this paper. In this discussion, we will describe the rationale for the sample size and our planned progression criteria to assess implementation feasibility as per Person and colleagues [69] guidance.

In quantitative analyses, there is little consensus on the appropriate sample size for a feasibility study, with guidance ranging from 12 per arm [70] to 50 per arm [71]. The justification for larger sample sizes in feasibility studies is often based around obtaining narrow standard deviations on outcome measures to maximise precision in a future power calculation [71]. However, there is disagreement over whether this is an appropriate method to inform power calculations as this would in turn increase the likelihood of identifying a statistically significant effect during the feasibility stage, which can be inappropriately reported, call into question the validity of the effect, and reduce the likelihood of a follow-up RCT [72–74]. As per the CONSORT extension [75], feasibility studies should focus on the acceptability of trial processes or an intervention, including recruitment, the time needed to collect and analyse data, and response rates to outcome measures. The overall evaluation of MMIEAD will require a multi-methods approach, with both quantitative and qualitative data. In qualitative analyses, for the process evaluation, simulations have shown that a sample size of 10 should identify 80% of problems within a complex intervention [76] while data saturation is likely to be reached at 12 interviews on average [41]. The principle of 10 plus five for data saturation outlines that a minimum of 10 interviews should be conducted, followed by potentially 5 consecutive interviews that present no new findings [77]. A formal sample size calculation is not appropriate for feasibility studies as the objectives do not include establishing the effectiveness of an intervention.

Progression to a definitive RCT will be determined by recruitment rates and the acceptability of the intervention for patients and staff. When developing progression criteria, the use of guidelines is suggested, rather than using strict thresholds, to allow for appropriate interpretation and exploration of potential solutions [75]. For example, Pearson and colleagues [69] recommend the use of a traffic light system with varying levels of acceptability. Therefore, compliance with the multimodal intervention will be assessed according to individual components (e.g. number of exercise sessions/tablet count) and thresholds of <50%, 50–80%, and >80%. Compliance of ≥50% of the specific intervention in ≥50% of patients will be considered acceptable; the appropriateness of which is outlined in previous multimodal interventions in cachexia management [78]. Progression to a full trial will be contingent on the acceptability of the intervention for both patients and staff regardless of recruitment rates which will be assessed within the qualitative process evaluation [66]. Any necessary modifications identified within the process evaluation to improve the intervention will be made prior to progression to a definitive trial [76].

### Strengths and limitations

The multi-phase study design, guided by the RE-AIM-PRISM framework [26, 27], will generate evidence of feasibility and implementation outcomes to build a strong definitive RCT and further refine our ToC model [20]. However, complex interventions contain several interacting components and present practical and methodological difficulties, such as standardising its design across two study sites, and adapting it to ensure it does not negatively impact on standard care [79]. Through our PRISM/RE-AIM design of MMIEAD, we have been circumspect in preparing for potential contextual implementation challenges [26]. The potential barriers and/or logistical challenges are described as follows, together with the mitigation strategies for overcoming them.We are aware that standard care may differ at site level; therefore, we plan to record these differences through the process evaluation.The on-site research team is small consisting of three staff with placement agreements for each site; one member of the research team will be responsible for intervention delivery, and therefore to enhance validity, this researcher will not be involved in interviewing participants from the intervention sites for the process evaluation.To ensure consistency in measurements, all on-site research team members have collectively conducted training in physical assessments (BIA, HGS, EFS, SPPB, MUAMC, TSF).We understand that the HCPs involved may experience staffing difficulties and unprecedented pressure; therefore, we have designed the trial to minimise unnecessary burden and support has been ongoing and delivered during online and in-person study set-up meetings.To ensure all member of our wider expert reference group stay informed about study progress, we have scheduled regular meetings and monthly newsletters with reminders and information related to the intervention, to ensure all members are kept updated.Patients receiving haemodialysis with or at risk of kidney cachexia are likely to be subject to multiple physiological challenges as their condition deteriorates which may affect adherence to MMIEAD. In planning this study, we have worked closely with consultant nephrologists who are our local collaborators to ensure that data collection points will coincide with planned dialysis, and routine clinical data already available (such as monthly blood tests performed in all dialysis patients as part of their standard care) will be used to minimise any potential additional burden to patients. Furthermore, PPIE representatives have provided expert patient knowledge and experience from inception taking account of any potential patient burden.

Overall, our preparation for these possible challenges will be ascertained during the process evaluation and their impact on the external validity of the study assessed through our multi-methods analyses using PRISM/RE-AIM dimensions and concepts.

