#### Blinding

Due to the nature of the intervention, neither patients nor HCPs can be blinded.

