### Data collection

To ensure consistency across the four study sites, all outcome assessors have undertaken standardised training before data collection begins, with refresher training provided as required. Harmonised data collection protocols, standard operating procedures, and uniform measurement tools will be used across all locations. Regular cross-site monitoring and fidelity checks will be conducted to ensure adherence to procedures and to minimise measurement error.

#### Phase 1

All eligible patients in both intervention arms and control arm will be required to complete baseline and follow up data at 6 weeks and 12 weeks. Longer-term survival (at 6 months and 12 months from the date of recruitment) will also be recorded. Adverse events (AEs) and serious adverse events (SAEs) will be reported using a standard procedure and relatedness will be determined by the clinical team as per our ethically approved reporting structure.

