### Analyses

#### Quantitative analysis (phase 1)

Quantitative data will be coded and entered into the Statistical Package for the Social Sciences (IBM SPSS Statistics Version 24). Data on participant eligibility, recruitment, refusal, and retention will be assessed as proportions and rates. Demographic characteristics and adherence to the intervention components will be reported with descriptive statistics as appropriate, for instance, reporting of mean standard deviation (SD) for interval scale variables and frequency/percentages for categorical variables. Differences between control and intervention groups at baseline will be assessed using chi-squared tests and independent *t*-tests. Potential effective outcomes will estimate the effect size and be analysed for mean change using pair sample *t*-tests to compare the difference pre and post intervention, and repeated measure analysis of variance (ANOVA) to consider interactions. However, given that this is a feasibility study, no inferences will be made regarding statistical significance, given that the sample size is not powered to make such assertions. Data from the 3-day food diary will be entered into Nutritics for diet analysis to estimate dietary protein and energy intake. By using Nutritics software (www.nutritics.com - version 3.1), this will enable analysis of compliance with food-based dietary guidelines [63].

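### The researcher who delivers the intervention is kept out of the intervention-site interviews, but not out of the effort- or judgement-dependent outcome assessments at the same sites

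*Protocol article*

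**What the plan says.** The Strengths and limitations section of the protocol article describes the team: "The on-site research team is small consisting of three staff with placement agreements for each site". Of these, "one member of the research team will be responsible for intervention delivery", and, with validity given as the reason, "this researcher will not be involved in interviewing participants from the intervention sites for the process evaluation". The next item in the same list reports that "all on-site research team members have collectively conducted training in physical assessments (BIA, HGS, EFS, SPPB, MUAMC, TSF" (the list of measures ends there). The deliverer belongs to that team.

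The Data collection section sets the assessor safeguards: "all outcome assessors have undertaken standardised training before data collection begins", with refreshers, common procedures and tools, and monitoring across sites. The Blinding section says "Due to the nature of the intervention, neither patients nor HCPs can be blinded" and does not mention outcome assessors.

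The outcome data have a stated use. Under Quantitative analysis (phase 1), "Potential effective outcomes will estimate the effect size", with pre-post change and repeated-measures ANOVA.

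**The concern.** The article sets a separation rule, gives validity as its purpose, and limits it to one type of data. The same reason applies to measures in which the assessor can influence the score. Handgrip is a three-attempt effort test. SPPB is a performance test that the Physical function section presents as supplying efficacy endpoints. The frailty scale, arm circumference and skinfold depend on scoring or on how the tape and calliper are placed and read.

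A person who has supported a patient through the programme may encourage more, or read more favourably, at follow-up. Control-site patients have no deliverer, so a shift of this kind would occur in one arm only. With two sites per arm, and no mention in the article of recording who assessed, it could not be separated from the effect of the intervention. What is at stake is the credibility of the effect sizes and of the group differences that the phase 3 analysis will present with confidence intervals.

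**Working it through.** **Step 1: the text side by side.**
- Delivery: one of three on-site staff.
- Barred from: process-evaluation interviews at intervention sites, and nothing else stated.
- Trained in physical outcome measures: all on-site staff, so the deliverer too.
- Assessor safeguards: training, common procedures and monitoring. These standardise technique. They do not make the assessor independent of delivery.
- Assessor masking: not stated.

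So the deliverer is qualified to assess outcomes at the intervention sites, and no sentence in the article rules it out.

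**Step 2: exposed assessments.** The plan's own sample size reproduces: 4 sites × 10 = 40, and 2 × 10 = 20 per arm. With visits at baseline, 6 and 12 weeks, the intervention sites have 20 × 3 = 60 assessments, of which 20 × 2 = 40 are after baseline. That is an upper limit on what the deliverer could do, not a forecast.

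**Step 3: scale.** The article gives no figure for assessor drift, so 0.1 to 0.3 SD is an assumption.
- Standard error of a standardised difference at 20 per arm, clustering ignored: √(1/20 + 1/20) = √0.1 = 0.316.
- Ratios: 0.1/0.316 = 0.32 and 0.3/0.316 = 0.95.
- With an assumed intracluster correlation of 0.05 and 10 per site: design effect 1 + 9 × 0.05 = 1.45, standard error √(0.1 × 1.45) = 0.381, ratios 0.1/0.381 = 0.26 and 0.3/0.381 = 0.79.
- The bias scales with the deliverer's share of assessments. At one third, 0.1 to 0.3 SD becomes 0.03 to 0.10 SD.

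These ratios refer to a difference at one follow-up visit. For change scores the standard error also depends on the correlation between visits, which the article does not give.

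**Step 4: which visits matter.** Write the assessor shift as b0 at baseline and b1 at follow-up. The bias in mean change is b1 − b0.
- If one person does all visits and the shift is constant, it cancels. If it grows as the patient becomes known, it does not.
- If the deliverer does baseline and a colleague does follow-up, at intervention sites only, the difference between the two raters enters the change in that arm only. A bar limited to 6 and 12 weeks would therefore permit a bias of the same structure. The bar has to cover all three visits.

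**Step 5: workload.** At the anticipated two patients per site per month, with all three visit types overlapping and no losses:
- Intervention sites: 2 × 2 × 3 = 12 assessments a month, or 6 for each of two colleagues.
- All four sites: 4 × 2 × 3 = 24 a month. The deliverer remains free to share the 12 at control sites.

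This reads the team as three people in total. If it means three at each site, cover is easier.

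**The case against.** The strongest reply is that this argues from silence in a condensed article. Being trained is not being assigned, and the operating procedures, which are not shown, may say who assesses whom. That stands as a limit on the claim. A reader might infer that the deliverer will carry out the 6- and 12-week assessments; the article does not say so. What remains is that the article does state a separation rule, and states it too narrowly for the data it goes on to use.

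Second, the interview rule may have its own purpose. The Qualitative analysis section is concerned with the bias of those who developed an intervention when they judge its acceptability, and acceptability bears on progression. This is fair, and it means the plan need not be read as conceding a general principle. It does not make the physical measures less open to influence.

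Third, the consequence is limited. The plan draws no conclusions about significance, says that establishing effectiveness is not an objective, and bases progression on recruitment and acceptability, with compliance thresholds. Suitability of outcome measures is judged largely by completion and burden, which score drift does not alter. A reader might infer that a biased effect size would leave the definitive trial too small. The article never says that this estimate will size that trial, and its Discussion notes disagreement over using feasibility data in that way. All of this stands.

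Fourth, the delivering role is only partly described. Physiotherapist and dietitian reviews are a large part of delivery, and the weekly calls fall to an unspecified trained team member. How closely the deliverer knows each patient is therefore uncertain.

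Finally, colleagues on the same small team would know the allocation, and patients are unblinded. Only the part of the bias that comes from delivering the intervention would be removed.

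**Conclusion.** The point holds in a limited form. The separation rule covers interviews but not the SPPB, handgrip, frailty, arm circumference and skinfold assessments for which the same person is trained. As written, the deliverer may assess patients they supported, at intervention sites only, and this could bias the effect sizes. BIA is less exposed.

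The size is unknown. The calculation shows only that an assumed drift of 0.1 to 0.3 SD, with the deliverer doing every follow-up, would stay below one standard error at this sample size, though at the upper end it would come close. The progression decision does not depend on it. It is not established that bias will occur, or that the effect sizes will be inflated. The change is still worth making because it is cheap and protects estimates that the plan intends to produce.

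**What to change.** Extend the sentence in Strengths and limitations so that the researcher delivering the intervention carries out neither process-evaluation interviews nor outcome assessments at the intervention sites, at baseline, 6 weeks or 12 weeks. One of the other two trained team members does these assessments, preferably the same assessor at all of a patient's visits. Record assessor identity at each visit and flag any unavoidable exception.

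The cost is rostering and one data field: about 12 intervention-site visits a month at planned accrual, with no new staff or training evident from the article. The downside is less scheduling flexibility in a three-person team whose visits are tied to dialysis sessions; the same colleagues may also be needed for the intervention-site interviews. Whether the roster works in practice cannot be settled from the article. How often exceptions are needed would itself be useful information for the definitive trial.

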## Data Availability

All information is included in the manuscript and supplementary file 1.

## Abbreviations

KDQoL-36: 36-item Kidney Disease Quality of Life scale
AEs: Adverse events
ANOVA: Analysis of variance
BIA: Bioelectrical impedance analysis
BMA: Body mass index
CCI: Charlson comorbidity index
CKD: Chronic kidney disease
CRN: Clinical research nurse
cRCT: Cluster randomised controlled trial
CRP: C-reactive protein
DHA: Docosahexaenoic acid
EFS: Edmonton Frail Scale
EPA: Eicosapentaenoic acid
eGFR: Estimated glomerular filtration rate
ESPEN: European Society for Clinical Nutrition and Metabolism
EWGSOP: European Working Group for Sarcopenia in Older People
FACIT-F: Functional Assessment of Chronic Illness Therapy
GCP: Good clinical practice
HGS: Handgrip strength
HRQOL: Health-related quality of life
HCPs: Healthcare professionals
KDOQI: Kidney Disease Outcomes Quality Initiative
MUAMC: Measures of mid upper arm muscle circumference
MRC: Medical Research Council
MUAMC: Mid upper arm muscle circumference
MAC: Mid-arm circumference
MODRUM: Modular resource use measure
MMIEAD: Multi-modal integrated intervention combining exercise, anti-inflammatory, & dietary advice
HSC: National Health Service (NHS)/Health and Social Care
NICE: National Institute of Clinical Excellence
NICTU: Northern Ireland Clinical Trials Unit
NICRN: Northern Ireland Clinical Research Network
PIS: Participant information sheet
PRISM: Practical, robust implementation, and sustainability model
QoL: Quality of life
RCT: Randomised controlled trial
RE-AIM: Reach, effectiveness, adoption, implementation, and maintenance
REC: Research Ethics Committee
SAEs: Serious adverse events
SPPB: Short Physical Performance Battery
SD: Standard deviation
SPSS: Statistical Package for the Social Sciences
TIDieR: Template for intervention description and replication
FAACT: The functional assessment of anorexia/cachexia therapy
ToC: Theory of change
TSF: Triceps skinfold
URR: Urea reduction ratio
FDA: US Food and Drug Administration
